## Abstract

**Background:**

Most incisions following surgery heal by primary intention, with the edges of the wound apposed with sutures or clips. However, some wounds may break open or be left to heal from the bottom up (i.e. healing by secondary intention). Surgical Wounds Healing by Secondary Intention (SWHSI) are often more complex to manage, and require additional treatments during the course of healing. There is significant uncertainty regarding the best treatment for these complex wounds, with limited robust evidence regarding the clinical and cost-effectiveness of different dressings and treatments; one such treatment is Negative Pressure Wound Therapy (NPWT) which is frequently used in the management of SWHSI. Previous randomised controlled trials (RCTs) of NPWT have failed to recruit to time and target, thus we aimed to conduct a pilot RCT to assess the feasibility of conducting a future, full-scale RCT.

**Methods:**

This pilot RCT will test the methods and feasibility of recruiting, randomising, and retaining participants into a larger trial of NPWT verses usual care for patients with SWHSI. Participants will be randomised to receive either NPWT or usual care (no NPWT) and will be followed up for 3 months.

**Discussion:**

This study will provide a full assessment of methods for, and feasibility of, recruiting, randomising, and retaining patients with SWHSI in a trial of NPWT versus usual care. On the basis of this pilot trial, a full trial may be proposed in the future which will provide additional, robust evidence on the clinical and cost-effectiveness of NPWT in the management of SWHSI.

**Trial registration:**

Clinical Trial Registry: ISRCTN12761776, registered on 10 December 2015 – retrospective registration.

**Electronic supplementary material:**

The online version of this article (doi:10.1186/s13063-016-1661-1) contains supplementary material, which is available to authorized users.

## Background

A substantial number of surgical operations are conducted in the NHS each year, with most involving an incision [1]. The edges of these incisions are often held together whilst healing occurs (primary closure); however, many surgical wounds break open or are left open to heal (healing by secondary intention). Surgical Wounds Healing by Secondary Intention (SWHSI) present a significant management challenge as they may remain open for many months and/or require multiple, additional treatments (e.g. prolonged hospitalisation, reoperation, infection management) [2]. As a result, management of SWHSI presents a significant financial burden to the NHS and also impacts substantially on patients’ quality of life.

There is much research evidence available to guide the management of SWHSI; however, as NICE reflected in their 2012 guidelines [3], there is a need for robust, experimental evidence to assess the most clinical and cost-effective dressings and treatments for surgical site management. Negative Pressure Wound Therapy (NPWT) has become a widely used intervention for SWHSI, albeit more frequently within acute rather than community settings [4]. NPWT devices apply negative pressure to a wound via a dressing which theoretically promotes wound healing by removing exudate and reducing infections [5]. The device is generally only used for part of the SWHSI treatment pathway rather than to the point of healing.

A Cochrane Review in 2015 [6] specifically investigated NPWT as a treatment for SWHSI; however, the review found only two trials eligible for inclusion. On the basis of this limited evidence and the fact that NPWT is widely used in the NHS to treat SWHSI, there is an urgent need to assess the effectiveness of this intervention in this specific patient population.

Previous trials of NPWT have struggled to recruit [7, 8] and so it would seem to be essential, before embarking on a full RCT, to assess the feasibility of conducting such research. Our study, therefore, seeks to ascertain the feasibility of conducting a full RCT in this area, specifically investigating the appropriate methods to use to collect meaningful and worthwhile data.

## Methods

### Design

This study is a pilot RCT conducted in three centres to test the methods and feasibility of a full RCT of NPWT compared with usual care (no NPWT) for SWHSI. Informed consent will be obtained from each patient prior to randomisation into the study. Eligible patients will be individually randomised to one of two treatment arms: (1) NPWT or (2) usual care (no NPWT).

The key objectives of this trial are to determine the methods and feasibility of conducting a larger RCT in this area. Specifically, this pilot trial will assess:Recruitment rate including willingness of participants to be randomised and whether recruitment is influenced by wound location or other factors, e.g. associated surgical specialityClinician willingness and ability to recruit and randomise participantsTesting of inclusion and exclusion criteriaFitness for purpose of data collection methods including across and between care settingsAbility of sites and clinicians to supply NPWT to intervention participants in a timely fashion, irrespective of care setting, and to assess any training requirementsAbility of community staff to manage participants randomised to NPWTSuitability of method of outcome ascertainmentAdequacy of duration of follow-upRates of withdrawal from treatment, response rates to questionnaires, attrition from the trial, and likely rates of missing data for outcomesAssessment of feasibility of blinding outcome assessors to treatment allocationAcceptability of trial documentation to nurses collecting study data in addition to treating patientsThe primary outcome for this pilot trial will be time to complete wound healing (full wound epithelialisation). However, this pilot study is not looking to detect a treatment effect but to determine the ability to recruit to, and collect high-quality data in, a full RCT. Secondary outcomes and methods of data collection are summarised in Table 1.

**Table 1 Tab1:** Secondary outcome measures

Secondary outcome	Measured by/using
Number of patients screened	Pre-Trial Screening Assessment Form
Number of patients eligible/ineligible	Pre-Trial Screening Assessment Form
Appropriateness of eligibility criteria and reasons for ineligibility	Pre-Trial Screening Assessment Form
Proportion of eligible patients consenting to participate (and whether type of wound/surgical speciality impacts on this)	Consent Form and Pre-Trial Screening Assessment Form
Time between randomisation and treatment start	Phase 1 Start of Treatment Form
Proportion of patients receiving randomised treatment within 48 h	Phase 1 Start of Treatment Form
Duration of Negative Pressure Wound Therapy (NPWT)	Phase 1 Start of Treatment Form and End of Phase 1 Treatment Form
Factors affecting timely delivery of randomised treatment	Non-immediate Use of NPWT Form
Wound dimensions	Assessment of Weekly Participant Events Form
Quality and completeness of data collected for date of healing	Assessment of Weekly Participant Events Form and Blinded Outcome Assessment Form
Patient-reported health-related quality of life	The Short Form (12) Health Survey (SF-12) [13] EuroQoL (EQ-5D) [14]
Cointerventions used and rate of treatment change	Investigator Baseline Case Report Form (CRF), Assessment of Weekly Participant Events Form, Phase 1 Start of Treatment Form, Phase 1 End of Treatment Form
Significant events (e.g. rehospitalisation, infection, reoperation)	Assessment of Weekly Participant Events Form
Adverse events	Adverse Event Form, Serious Adverse Event Form, Adverse Event/Serious Adverse Event Follow-up Form
Response rates	Proportion of participant self-report measures returned
Withdrawal rates	Change of Status Form
Treatment change including change from NPWT for intervention participants, reasons for changes and changes to NPWT	Surgical Wounds Dressing Change Form, End of Phase 1 Treatment Form and Assessment of Weekly Participant Events Form
Resource use	Resource Use Questionnaire (3-month Participant CRF)
Missing data rates	Missing responses
Healing rates	Assessment of Weekly Participant Events Form, Blinded Outcome Assessment Form
Blinded outcome assessment	Blinded Outcome Assessment Form
Participant opinion on trial participation	Likert Scales (3-month Participant CRF)
Self-reported wound pain	Weekly text messaging Visual Analogue Scales (baseline, 2-week, 1-month and 3-month Participant CRFs) Brief Pain Inventory (BPI) (baseline, 2-week, 1-month and 3-month Participant CRFs) [15]
Wound progress	Photographs Wound tracings Depth measurements

Participants will be followed up every 1–2 weeks, depending on feasibility, for clinical outcome assessment. Participant-completed questionnaires will be completed at baseline, 2 weeks, 1 month, and 3 months post randomisation. Participants will be followed from randomisation to trial exit, which is deemed to be 3 months after randomisation, or loss to follow-up or death (if before this time). Participant flow through the trial and the schedule of study activities are displayed in Fig. 1.

**Fig. 1 Fig1:**
[figure not shown]
Participant flowchart and schedule of activity. Outlining participant flow through the study and outcome measurement completion time points

### Inclusion and exclusion criteria

#### Inclusion

Our target population will be patients aged 18 years and over who are able to give full informed consent and who: are receiving care from either Hull and East Yorkshire Hospitals NHS Trust, Leeds Teaching Hospitals NHS Trust or Leeds Community Healthcare NHS Trust; have a SWHSI which could be reasonably treated with NPWT or wound dressings; have a SWHSI which is considered ready for NPWT (i.e. minimum 80 % viable tissue or thin layer of slough requiring no further debridement); and are receiving adequate nutrition (as assessed by the senior nurse responsible for nursing care).

#### Exclusion

We will exclude patients who: are unable to give informed consent; have limited life expectancy (e.g. are undergoing end-stage palliative care); have an active systemic infection; have already received NPWT on their current SWHSI, are currently receiving NPWT or received NPWT whilst in theatre for the surgery resulting in their SWHSI; have inadequate haemostasis or are at risk of bleeding; have chronic wounds such as pressure or foot ulcers which are nonsurgical in origin but which have been surgically debrided (we regard these patients as a distinctly different subgroup); are unwilling to have wound photographs taken; or are currently or have previously participated in a research study within the last 4 weeks.

Patients will also be excluded if they have any of the following wound characteristics present: unclear undermining in the wound cavity precluding use of NPWT; necrotic tissue or eschar; malignant tissue; exposed blood vessels and/or organs, anastomotic sites, and/or nerves (including cases where abdominal fascia is open); or located where a vacuum seal cannot be obtained (in the opinion of the treating clinician).

### Recruitment

Patients will be recruited from both acute and community settings within Hull and Leeds; however, we anticipate that most participants will be recruited from acute settings. The pilot trial will be preceded by promotion of the study with surgeons and nurses in both settings.

All patients who experience a SWHSI (at any point following surgery) will be screened for trial eligibility by their clinical care team. Potential participants will then be approached with further details of the study by surgical or nursing staff (clinical or research) during ward rounds, routine care or home visits, depending on patient circumstance.

Potential participants will be provided with a patient information sheet and will be given at least 24 h to consider their involvement in this research. Patients will then have the opportunity to discuss the study with the research team prior to completing the study consent form.

We aim to randomise 50 patients for this pilot trial over a 7-month period. As evidenced by Edwards et al. in 2002 [9], nonconditional, monetary incentives are shown to double response rates to postal questionnaires; participants will, therefore, be sent a £5 unconditional cash token with their final questionnaire (at 3 months post randomisation). Participants who consent to receiving weekly text messages, and provide a mobile telephone number to facilitate this, will also be reimbursed £5 to cover any costs incurred in responding to weekly pain assessment text messages.

### Randomisation

Patients will be randomised into one of two arms: (1) NPWT or (2) usual care (no NPWT) on a 1:1 basis. To remove the potential for selection bias, allocations will be concealed through use of a central randomisation service implemented by an independent member of staff at the York Trials Unit, University of York. Study sites will contact a remote telephone service to provide details of the participant and to receive details of the treatment allocation. Randomisation will be conducted using a pregenerated sequence of random permuted blocks with stratification by wound area (<28 cm^2^, ≥28 cm^2^).

Due to the nature of the intervention it is not possible to blind participants or health care professionals to trial treatment. Feasibility of blinded outcome assessment of healing will, however, be assessed as part of this trial. Assessors blind to trial treatment allocation will be provided with copies of wound photographs and will be asked to confirm whether (1) they deem the wound to be healed (full wound epithelialisation), and (2) they believe they know the allocated treatment allocation.

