### Sample size

As this is a pilot trial, and the primary objective is to determine measures of feasibility and acceptability rather than to detect a treatment effect, a formal sample size calculation has not been conducted. We will, however, aim to randomise approximately 50 patients as a means to assess recruitment, randomisation, and retention of participants.

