### Statistical analysis

A full statistical analysis plan for primary and secondary analyses will be generated prior to completion of recruitment for this trial. The Trial Management Group and the Data Monitoring and Ethics Committee (DMEC) will review this prior to commencement of outcome analysis. During the trial regular reports will be prepared for the DMEC with regards data quality and safety.

The analyses will be conducted following the principles of intention-to-treat. All outcomes will be summarised using descriptive statistics overall and by trial group.

The primary clinical outcome of time to healing will be presented using Kaplan-Meier curves for interest only, recognising that the study is not powered to detect clinically important treatment effects. This analysis will be conducted using blinded outcome assessment dates of healing if possible. A Cox proportional hazards regression analysis will be conducted, subject to sufficient data, to investigate the inclusion of additional covariates shown to be important in an earlier SWHSI cohort (e.g. contamination level of surgery, wound infection), along with the stratification factor (baseline wound size) used in the randomisation for this trial. The impact of SWHSI history, location of SWHSI on the body and infection at any time during follow-up (as a time dependent covariate) will also be explored.

Cost-effectiveness will be explored by calculating a mean total cost per trial arm using resource use and relevant unit costs for each participant. Should sufficient data be available, EuroQoL 5 dimensions (EQ-5D) questionnaire data will be used to calculate a mean quality-adjusted life year (QALY) for each trial arm.

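### As described, the blinded assessors' allocation question records whether they think they know the arm, but not which arm, so it measures perceived unblinding and not its accuracy

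*Protocol article*

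**What the plan says.** The Randomisation section of the protocol article explains that participants and health care professionals cannot be blinded, and continues: "Feasibility of blinded outcome assessment of healing will, however, be assessed as part of this trial". Assessors kept unaware of allocation "will be provided with copies of wound photographs and will be asked to confirm whether (1) they deem the wound to be healed", and, as the second numbered item, whether "they believe they know the allocated treatment allocation". Nothing is said about which arm they believe it to be, or why.

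The Design section lists the feasibility of blinding outcome assessors among the pilot's objectives. Table 1 names the instrument, the "Blinded Outcome Assessment Form", but its items are not reproduced. Under Statistical analysis, the article says of the healing curves: "This analysis will be conducted using blinded outcome assessment dates of healing if possible".

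**The concern.** With patients and treating staff unblinded, reading photographs is the only protection the article describes against biased judgement of healing. Whether photographs hide the treatment is therefore something that a full trial needs to learn from this pilot, which by its own account does not set out to detect a treatment effect.

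The second item is a yes/no question about the assessor's own belief. A yes can mean that the photograph gave the arm away, or that the assessor was confident and wrong. These have different consequences. The first means that masking by photograph has failed for that assessment. The second means that the arm was not revealed, though a mistaken belief may still colour the reading. If the guess is never recorded, no later analysis plan can recover it.

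**Working it through.** The article gives no figure on this point, so there is none to reproduce. The check is whether accuracy of belief can be identified from the item as described.

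**Inputs**
- Sample: "aim to randomise approximately 50 patients as a means to assess recruitment, randomisation, and retention of participants" (Sample size).
- Allocation 1:1 (Randomisation), so about 50/2 = 25 per arm.
- Observed per arm: k, the number of assessments in which the assessor claims to know.
- Not observed, as described: c, the number of those k beliefs that are correct.
- Assumption: one assessment per participant, so n = 25 per arm. The values of k below are illustrative, because the article gives no expected yes rate.

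**Formula**

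Bang's index for an arm = (correct - incorrect)/n = (c - (k - c))/n = (2c - k)/n.

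Since c may be any whole number from 0 to k, the index may lie anywhere from -k/n to +k/n.

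**Range left open by the yes/no item, n = 25**

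| Claim to know (k) | Share | Lowest index | Highest index |
|---|---|---|---|
| 0 | 0% | 0 | 0 |
| 5 | 20% | -0.2 | +0.2 |
| 10 | 40% | -0.4 | +0.4 |
| 15 | 60% | -0.6 | +0.6 |
| 20 | 80% | -0.8 | +0.8 |
| 25 | 100% | -1.0 | +1.0 |

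**One row worked through.** Take k = 15.
- All correct: (15 - 0)/25 = 0.60, which is substantial unblinding.
- Split 8 to 7: (8 - 7)/25 = 0.04, which is close to chance.
- All wrong: (0 - 15)/25 = -0.60.

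The item as described records 15 of 25 in all three cases. Tabulating yes answers by arm does not resolve this, because a yes in either arm may be right or wrong.

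**What the item does measure.** The proportion claiming to know can be estimated. With 50 assessments, Wilson 95% intervals are:
- 5/50 = 10%, interval 4% to 21%
- 10/50 = 20%, interval 11% to 33%
- 25/50 = 50%, interval 37% to 63%

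Perceived unblinding is therefore measurable. The accuracy of the belief is fixed only at k = 0, and the range left open widens in proportion to k.

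**The case against.** **The form may already ask.** The article does not say that these two items are the only ones. It condenses a fuller protocol, and the form is named but not shown. A follow-up item on the believed arm could exist. This stands, and the point is limited to the item as the article describes it. It does not remove the point, because the article sets out the assessor's task as two numbered items and the second stops short of the guess.

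**The data still say something about blinding.** A reader might infer that the pilot cannot show at all whether blinding worked. The documents do not support that. A low yes rate would favour successful blinding: no yes answers fixes the index at 0, and 5 of 25 confines it to within 0.2 of 0. The loss is serious only when many assessors claim to know.

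**The objective is feasibility, not a formal blinding test.** This also stands. Feasibility includes whether photographs are obtained, can be judged and yield healing dates, and this item affects none of that. The article promises no blinding index.

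**The healing curve.** A reader might also infer that the curve could rest on whichever source of healing dates proves convenient. The text does not bear that out. The Statistical analysis section states a preference for blinded dates, and Table 1 draws healing rates and the quality of healing-date data from both the weekly events form and the blinded assessment form. How the preference is applied, and whether a second curve is shown, are properly left to the analysis plan.

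**The consequence for results is small.** The curves are for interest only, and the article notes that "a formal sample size calculation has not been conducted", so no power or error rate is affected. That is correct. What is at stake is what the pilot can tell a full trial about masking.

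**Conclusion.** The point holds as a limited measurement weakness. As described, the second item captures whether assessors believe they know the allocation and cannot separate correct beliefs from mistaken ones. The uncertainty it leaves in Bang's index is plus or minus k/n per arm: nil if no one claims to know, 0.6 either way at 15 of 25, and total at 25 of 25. This limits what the pilot can conclude on a stated objective, most of all in the situation where the answer matters most.

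The conclusion assumes that the form contains no further item on the believed arm. The figures assume about 25 assessments per arm, one per participant; with repeated photographs n would change but the bounds keep the same form. The yes rates are illustrative.

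**What to change.** Check the blinded assessment form first. If it already records the believed arm, stating so in the protocol is enough.

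If it does not, replace the second item with: *Which treatment do you think was allocated: NPWT, usual care, or don't know?* Add a short free-text reason, so that cues in the photographs can be identified. Have it answered after the healing judgement is recorded, so that the guess cannot influence that judgement. Report correct, incorrect and don't-know answers by arm, or Bang's index by arm.

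The cost is one changed form item and one small table. The trial was still recruiting when the article was submitted, with follow-up due to end on 30 September 2016 and analysis to begin in October 2016. Because assessors work from copies of photographs, the item can be added without further contact with patients. The drawback is that photographs already read may need the item asked again.

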### Sample size

As this is a pilot trial, and the primary objective is to determine measures of feasibility and acceptability rather than to detect a treatment effect, a formal sample size calculation has not been conducted. We will, however, aim to randomise approximately 50 patients as a means to assess recruitment, randomisation, and retention of participants.

### Interventions

#### Experimental group: Negative Pressure Wound Therapy

There are several NPWT systems available within the NHS; however, for the purposes of this trial we originally permitted the use of the following CE-marked products currently used in acute and community settings in Hull and Leeds: (1) V.A.C.® (KCI), and (2) Renasys® (Smith and Nephew). A further device (PICO® – Smith and Nephew) has subsequently been added as a trial device in a recent protocol amendment.

NPWT treatments consist of a vacuum pump into which a disposable plastic canister is placed to enable wound exudate to be collected. The canister is attached to pressure resistant tubing to create an airtight seal. The wound to be treated is filled with a suitable dressing (foam or gauze) along with a nonadherent layer, if required, to protect blood vessels or organs and/or to prevent dressing adherence.

In this trial, the choice of machine and duration of NPWT will be decided by the treating health professional in conjunction with the participant and nurse. Pressure cycles and dressing change frequency will be completed as per standard practice and recorded. The only stipulation with regards NPWT use is that this must be clinically appropriate. When not being treated with NPWT, participants in this arm of the trial will be treated as per usual care.

